#### Preparation

All centres had already been extensively trained in the main diagnostic assessments (see below) for the purpose of the dementia diagnostic pilot study [5]. Two further one week project planning meetings were held, in London for the PIs from Cuba, Brazil, DR, China and India and in Caracas for the Venezuelan, Mexican, Peruvian and Argentinean teams. One day follow-up meetings were held for all PIs in Barcelona and Dominican Republic. A standardized operating procedures manual covers every aspect of the training and field procedures.

#### Interviews and measures

All assessments were carefully translated into the relevant local languages (Ibero-American Spanish, Brazilian Portuguese, Tamil and Mandarin). Interviews were generally carried out in participants' own homes. This was a comprehensive one phase survey – all participants receive the full assessment, lasting approximately 2–3 hours.

##### 1) Outcome – The diagnosis of dementia

Our previously published 10/66 dementia diagnosis algorithm [5] requires

(i) A structured clinical mental state interview, the Geriatric Mental State, which applies a computer algorithm (AGECAT)[74], identifying organicity (probable dementia), depression, anxiety and psychosis and,

(ii) A cognitive test battery comprising a) the Community Screening Instrument for Dementia (CSI'D') COGSCORE [75] (incorporating the CERAD animal naming verbal fluency task), and b) the modified CERAD 10 word list learning task with delayed recall [76] and

(iii) An informant interview the CSI'D' RELSCORE [75], for evidence of cognitive and functional decline

(iv) an extended informant interview, the History and Aetiology Schedule – Dementia Diagnosis and Subtype (HAS-DDS), a modification of the earlier HAS [77], providing more detailed information on onset and course of a possible dementia syndrome

v) The NEUROEX, a brief fully structured neurological assessment with objectified quantifiable measures of lateralising signs, parkinsonism, ataxia, apraxia and primitive 'release' reflexes [78,79].

(vi) Behavioural and Psychological symptoms of dementia (BPSD); assessed using an informant questionnaire, the Neuropsychiatric Inventory (NPI-Q) [80].

Final dementia diagnoses is made in two ways. The main dementia outcome is defined as those scoring above a cutpoint of predicted probability of DSM IV Dementia syndrome [81] from the logistic regression equation developed in the 10/66 international pilot study, using coefficients from the GMS, CSI-D and 10 word list learning tasks [5]. The second approach involves the direct application of research diagnostic criteria for DSM IV and for the following dementia subtype diagnoses; NINCDS-ADRDA Alzheimer's disease criteria [82], NINDS-AIREN vascular dementia criteria [83], and Lewy Body Dementia [84]. The clinical assessment identifies other prevalent conditions relevant to the differential diagnosis of dementia and dementia sub-type: psychosis, depression, anxiety disorder, alcoholism, epilepsy and stroke. Circularity in further validation of these diagnoses can only be avoided by focusing upon their predictive validity. Thus, a diagnosis of dementia should lead to further cognitive and functional decline, and not recovery.

##### 2) Blood sample protocol

Fasting blood samples were sought from all participants in all centres other than India, China and Nigeria, necessitating revisits for phlebotomy first thing in the morning. 15 mls of blood was drawn and distributed as follows; one 5 ml plastic EDTA for haematology and DNA extraction or storage, one 2.5–3 ml Fluoride Oxalate bottle for glucose and the remainder (approx 8 ml) to a clot bottle for biochemistry. Samples were transferred immediately to the laboratory for haematological and biochemical analysis (see below). Serum obtained from centrifuging the clot sample was divided into aliquots and fresh frozen at -20 C. For the DNA collection, in Cuba and Venezuela the EDTA samples are processed and DNA extracted immediately. In Dominican Republic the EDTA sample is frozen at -20 C. In Peru, Argentina and Mexico blood is collected onto FTA Elute (Isocode) cards. Each 3 mm punch yields 20 × 50 ul PCR reactions (100 × 10 ul) so one card set generates 640 × 50 ul PCR reactions.

##### 3) Genotyping

DNA will be extracted and stored from all seven centres. APOE genotyping will be conducted on all samples, and 60 SNPs informative for African/European ancestry admixture will be genotyped from centres where admixture is relevant (Cuba, Dominican Republic, Mexico, Peru and Venezuela). The 60 SNPs will be chosen from the panel assembled by [name] at Penn State and [name] at NCI [85]. With 60 SNPs that have average 40% information content for ancestry, we shall be able to estimate three-way individual admixture proportions with a standard error of less than 0.1.

##### 4) Principal exposures – environmental

This information was elicited from participants; with informants also interviewed for those with communication difficulties arising from dementia, severe mental illness, deafness or mutism.

###### 4.1 Sociodemographic status

a) age, living circumstances (complete list of coresidents with ages and relationships), marital status, education, literacy, religion affiliation and practice, community social activity, social support, social network

b) Socio-economic status – best occupation (self and spouse), current occupational status, income and sources of income, household assets index, food insecurity

c) Migration status – Rural or urban residence across the life course. Age when moved,

###### 4.2 Health status

a) self reported global health,

b) self-reported diagnoses (stroke, diabetes, hypertension, heart disease, hypercholesterolaemia, TB, malaria, and cystercicosis) and treatments for these conditions

c) a self-reported list of 12 commonly occurring physical impairments [86];

d) activity limitation and participation restriction measured by the WHO-DAS II [87], specifically developed by the WHO as a culture-fair assessment tool for use in cross-cultural comparative epidemiological and health services research.

e) direct physical assessments – pulse rate, systolic and diastolic resting blood pressure (average of two, sitting and standing), waist circumference, waist/hip ratio, walking test (5 metres walk, turn and return – timed and paces counted).

f) Reproductive status (for women) – menarche, menopause, reproductive period, number of children

###### 4.3 Biological assessments

a) Physical assessments – pulse rate, systolic and diastolic resting blood pressure (average of two, sitting and standing), waist circumference, waist/hip ratio, leg length, height, skull circumference, walking test (5 metres walk, turn and return – timed and paces counted).

b) Haematological tests; full blood count (haemoglobin, haematocrit, differential, MCV, MCH, MCHC).

c) Biochemical tests; fasting glucose, fasting total cholesterol and sub-fractions, triglyceride, albumin, total protein.

These data collected allow us to identify metabolic syndrome according to the criteria proposed by the Third Report of the National Cholesterol Education Program (NCEP – ATP III) : presence of three or more of the following; 1. Central obesity as measured by waist circumference: Men > 40 inches, Women > 35 inches. 2. Fasting triglycerides >= 150 mg/dL. 3. HDL cholesterol: Men < 40 mg/dL, Women< 50 mg/dL. 4. Blood pressure >= 130/85 mmHg. 5. Fasting glucose >= 110 mg/dL

###### 4.4 Risk exposures

a) specific dementia risk factors – head injury with loss of consciousness, family history of dementia, previous depression, leg length, height, skull circumference,

b) Lifestyle and cardiovascular risk factors – alcohol use (volume and frequency currently and before the age of 60), lifetime smoking (never, ever and current smokers and pack year calculation), diet (intake of fish, meat and fruit and vegetables; food insecurity), exercise and activity levels now and in earlier life.

##### 5) Measures of care arrangements, and impact of providing care on caregivers

These measures have been refined and validated in the 10/66 group's pilot studies[9,12].

a) Economic impact was assessed using the Client Service Receipt Inventory [88], a comprehensive assessment of direct and indirect economic costs for mental health services, adapted for use in the developing world. It elicits information on type and cost of accommodation, income (from all sources) for the person with dementia and the principal caregiver, the occupation of the caregiver, the extent to which the caregiver had cut back on or stopped work in order to provide care, unpaid care provided by family or others in the community, paid care inputs and their costs, and the use (and associated costs) of a variety of health care services; hospital services (inpatient and outpatient); government community health services (general practitioner, nurse, community health worker, other health worker); private doctor; dentist; time and duration of visits, out of pocket costs for the consultations and medications, time taken to travel, cost of travel.

b) Practical impact – contact time between caregiver and cared for person [89], whether or not care was being provided. Time spent by the caregiver in the last 24 hours in specific caregiving activities [90]; communicating, using transport, dressing, eating, looking after one's appearance, and supervising,

c) Caregiver perceived strain – the Zarit Burden Interview (ZBI) [91-93] with 22 items that assess the caregiver's appraisal of the impact their involvement has had on their lives.

d) Caregiver mental health (the Self Reporting Questionnaire 20) [94].

e) Behavioural and Psychological symptoms of dementia; the Neuropsychiatric Inventory (NPI-Q)[80]

#### Data management

In Cuba, all data was collected directly onto laptop computers using computerized Spanish questionnaires driven by EpiData (version 2.0) software. These questionnaires, developed by the 10/66 group incorporate conditional skips, and interactive checking of data consistency. In other Hispanic centres, data was collected onto paper and double data entered onto the same EpiData files. Chinese and Indian centres used English language data entry files. Identical EpiData files in all centres facilitates data processing, data merging and archiving. Data is extracted into SPSS, and all processing (cleaning, processing of derived variables and running of 10/66, DSMIV dementia and other diagnostic algorithms) is carried out using SPSS batch files. The end result is a cleaned, processed and labelled data set that can be exported into other statistical programs for further analysis.

#### Ethical issues

Participants were recruited following informed signed consent. Persons with dementia who lack capacity for consent were recruited on the basis of a relative's signed agreement. Illiterate persons were read the information sheet and consent form, and invited to express their consent verbally, which was witnessed. Participants were invited to make a gift of genetic material (blood) to the local research institutions who act as custodians in whom are vested full rights for scientific and commercial exploitation, subject only to limitations upon the phenotypes to be investigated. Studies were approved by local ethical committees as well as by the ethical committee of the Institute of Psychiatry, King's college London.

### Incidence phase

#### Tracing participants

Response rates for the baseline surveys were generally high, ranging from 74 to 98% (see Table 1). For the follow-up, which was pre-planned at baseline, we have collected the names, addresses and telephone numbers of three non co-resident local relatives, friends or neighbours who can be contacted to help trace the participant if they are not at their original address. The population in each of the settings where we are working is stable. Apart from a likely 6% per annum attrition from mortality, we anticipate a very high follow-up rate, in excess of that typically achieved in cohort studies in developed countries. All methods, procedures and logistics are well established from the 10/66 baseline surveys.

#### Protocol

The interviews for the incidence phase largely involve a repeat of the one phase dementia diagnostic protocol previously described, with the aim of identifying incident dementia. We will modify the DSMIV algorithm to incorporate cognitive test and informant data from baseline into the direct determination of cognitive and functional decline. We will also reassess risk exposures that may have changed over the three years since baseline. All participants will receive the same comprehensive assessment, very similar to that administered in the baseline survey, regardless of their baseline status. Those with dementia at baseline will have been at risk for stroke, and we will repeat dementia assessments to assess course and outcome and to validate baseline diagnoses. We will also review care arrangements, dependency and indices of caregiver strain. Interviewers will be blinded to baseline diagnostic status.

### Interviews and data collection

#### Mortality

For those who died between baseline and follow-up (information ascertained on follow-up visit) we will complete a verbal autopsy interview with a co-resident, relative or other person well-placed to know the circumstances of death, using methods developed and validated by the 'Million Deaths' project for use in India [95,96] to identify underlying cause according to ICD10 criteria. The interview takes 30–45 minutes using structured questions and an open-ended narrative, with a symptom list to assist attribution. Cause of death is allocated by the consensus judgement of two physicians. The approach is valid for use up to three years post-mortem. We will also attempt to ascertain whether the participant had an onset of dementia before death, using the standard 10/66 informant assessment.

#### Stroke

We also include a two phase clinical protocol designed to identify incident stroke. All those claiming (by participant or informant report) to have experienced a stroke in the interval between assessments, and all those with suggestive neurological signs (asymmetric long tract signs, dysphasia, marked gait disturbance) not apparent at baseline will be offered physician assessment including physical examination, clinical history, and examination of clinical notes and investigations where available ('cold pursuit'). We will then seek consensus diagnosis from two local independent experts. Stroke diagnosis (ARIC criteria [97]) require

a) evidence of sudden or rapid onset of neurological symptoms

b) lasting for more than 24 hours or leading to death,

c) in the absence of evidence for a nonstroke cause (brain trauma, neoplasm, coma attributable to metabolic disorders or disorders of fluid or electrolyte balance, CNS vasculitis or infection, and peripheral neuropathy).

In our baseline data set 96% of those who reported a stroke had a clinical diagnosis, 81% from a specialist. However, neuroimaging will not routinely be available, and we cannot be confident that we will have enough information to attribute stroke sub-type with confidence. Silent brain infarctions (picked up by neuroimaging without clinical symptoms and signs) will not be included.

#### New retrospective exposure data (not collected at baseline)

Number of remaining teeth, use and quality of dentures

Use of lipid-lowering agents

Calf circumference

Weight (using digital scales)

Grip strength

Interviewer assessment of mobility (bedbound/chairbound/housebound/limited mobility outside/unrestricted mobility

#### New biochemical assays

Fresh frozen serum from baseline collections are available in Cuba, DR, Venezuela, Peru, Argentina and Mexico. We will use these to investigate associations between micronutrient deficiency and dementia/AD. We will use a nested incident case control design whereby for each incident case, we shall select three controls at random from among those matching for age, gender and education, who were free of dementia at the time of onset for the case. Assuming 219 incident cases in these six centres (see below) this will imply 876 samples to be assayed for Vitamin B12, folate, TSH and T4. Routine assays will be carried out by local laboratories, but procedures will be standardised as far as possible. Fresh frozen serum stored at -20 C is appropriate for these analyses.

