For the nested incident case-control study we estimate that 219 cases and 657 matched controls will be available. Given the matching, all analyses will be carried out using conditional logistic regression (Stata 8.2). For exposure prevalences ranging from 5% (lowest realistic estimate of prevalence for folate deficiency and subclinical hypothyroidism) to 40% (likely prevalence of vitamin B_12 _deficiency) such a comparison will have good (80%) to excellent (90%) power for detecting policy-relevant effects (Table 4).

**Table 4 T4:** Minimum detectable effect size (OR) for matched incident case-control comparison

**Exposure Prevalence Power**	**5%**	**10%**	**15%**	**40%**
80%	2.4	2.0	1.8	1.6
90%	2.7	2.2	2.0	1.7

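### The nested case-control rule matches on age, gender and education but not on centre, so as written most matched pairs would compare different countries and local laboratories

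*Protocol article*

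**What the plan says.** The protocol article, under New biochemical assays, states where the serum comes from: "Fresh frozen serum from baseline collections are available in Cuba, DR, Venezuela, Peru, Argentina and Mexico". For each incident case it will "select three controls at random from among those matching for age, gender and education", with the further condition that controls are free of dementia when the case has its onset. On the assays it says: "Routine assays will be carried out by local laboratories, but procedures will be standardised as far as possible". The volume is given as: "Assuming 219 incident cases in these six centres (see below) this will imply 876 samples to be assayed".

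Under Power and sample size considerations the same numbers return ("we estimate that 219 cases and 657 matched controls will be available") and the analysis is fixed: "Given the matching, all analyses will be carried out using conditional logistic regression". No centre term is stated. Nothing elsewhere in the article keeps a matched set within a centre, plans a central assay, or plans calibration across laboratories.

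**The concern.** Conditional logistic regression removes only what is constant within a matched set. If a set may contain participants from several countries, neither country nor laboratory is constant within it.

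The article itself makes country a plausible confounder:

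- **Outcome.** Primary objective 5 estimates incidence by centre. The background section on developed/developing country differences suggests that dementia frequency may track historical infant mortality, which it lists from 40/1000 in Cuba to 109/1000 in Peru.
- **Exposure.** The same section ties folate and B12 deficiency to poverty, diet and economic crisis, and calls the iodine content of salt poorly regulated. The Discussion says exposure prevalence may differ between regions.
- **Measurement.** Each country uses its own laboratory. Baseline collection ran from mid-2003 (Cuba) to late 2006 (Mexico), so serum storage time may also differ by country.

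Hypotheses (b) and (c) of objective 5, on micronutrients and subclinical hypothyroidism, rest on this comparison.

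**Working it through.** **1. The plan's own figures.** Table 2 cases: 55 + 37 + 37 + 30 + 30 + 30 = 219. Controls: 219 × 3 = 657. Samples: 219 × 4 = 876. All agree with the text. Table 4 reproduces to within 0.1 with a matched 1:3 calculation (Dupont's method), assuming two-sided alpha 0.05 and a case-control exposure correlation of 0.2: 2.45/2.00/1.82/1.60 at 80% power and 2.78/2.21/1.99/1.72 at 90%. The sample size is not in question.

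**2. Share of same-country pairs under the rule as written.** This treats age, gender and education as similarly distributed across countries (assumed). Formula: sum over countries of (share of cases × share of control pool).
- Pool = dementia-free at baseline: (55×2670 + 37×1780 + 37×1800 + 3×30×1800) / (219×11650) = 441,310 / 2,551,350 = 0.173.
- Pool = person-years: (55×6730 + 37×4488 + 37×4490 + 3×30×2906) / (219×24426) = 963,876 / 5,349,294 = 0.180.

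So about 82–83% of pairs cross countries.

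**3. Null odds ratio with Table 2's case mix.** Group A is Cuba, DR and Venezuela; group B is Mexico, Peru and Argentina. A supplies 129/219 = 0.589 of cases, but 6250/11650 = 0.536 of the dementia-free pool and 15708/24426 = 0.643 of person-years. With no true effect and country unmatched, exposure is independent between case and control, so OR = a(1−b) / [b(1−a)], where a and b are the centre-weighted prevalences in cases and controls. Prevalences are assumed.
- 60% in A, 20% in B, dementia-free pool: a = 0.20 + 0.40×0.589 = 0.436; b = 0.20 + 0.40×0.536 = 0.415; OR = 1.09. Prevalences reversed: 0.91.
- Same prevalences, person-year pool: 0.92; reversed: 1.10.
- 50% versus 30%: 0.96 to 1.05 over the same choices.

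**4. Null odds ratio if incidence differs between the groups (assumed), equal follow-up.** With A at twice B's rate, A's case share = 2×6250 / (2×6250 + 5400) = 0.698.
- 50% versus 30%: a = 0.440, b = 0.407, OR = 1.14; rejection in the spurious direction about 13%.
- 60% versus 20%: a = 0.479, b = 0.415, OR = 1.30; rejection about 39%. Nominal is 2.5%.
- At 1.5 times the rate: 1.08 and 1.17.

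The opposite direction can be shown with a 53/47 split (4668 of the 8811 available for interview are in A) and assumed prevalences of 25% in A and 55% in B: b = 0.53×0.25 + 0.47×0.55 = 0.391. With A at twice the rate, A's case share = 1.06/1.53 = 0.693, a = 0.342, OR = 0.81. With A at half the rate, OR = 1.23. Table 2's own cases per person-year are 129/15708 = 0.0082 in A and 90/8718 = 0.0103 in B, a ratio of 1.26. Putting 1.26, in either direction, into the same example gives 0.93 or 1.07.

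**5. Attenuation.** Take a true within-centre OR of 2.0 and cases with the same country mix as controls (equal overall incidence). Case prevalence within a centre is 2p/(1+p).
- 60% versus 20%: a = 0.536×0.750 + 0.464×0.333 = 0.557; b = 0.415; OR = 1.77.
- 50% versus 30%: OR = 1.94.

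This depends on overall incidence being equal. If instead the unexposed rates are equal across countries, case shares become proportional to pool share × (1+p), and the pooled OR returns to 2.00.

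**6. Room for within-country controls.** Available participants per expected case: 1329/37 = 36 (DR, the lowest) to 1381/30 = 46. These are country totals before restricting to stored serum and to matches on age, gender and education.

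**The case against.** The fair counter-argument is that the article lists matching factors without saying that sets cross countries. Sera and assays are handled locally, so within-country sampling may have been intended, and a full protocol may say so. This limits the point to the rule as written: a reader might infer that the investigators chose cross-country sets, and the article does not show that. It does state a sampling rule, however, and someone following it literally would draw across countries. Elsewhere, for the randomised trial, the article says explicitly when balance is wanted within each centre.

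A second objection also stands in part. The article gives no covariate list and does not exclude a centre term. If sets do cross countries, centre varies within sets and can be fitted in the same conditional model. A reader might infer that the confounding is locked in once sets are drawn; that is not supported. Adjustment would recover much of it, at some loss of efficiency, but would not by itself correct misclassification at laboratory-specific cut-points.

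Third, a reader might take 0.81 or 1.23 as the expected bias. The documents do not support that. The plan assumes one incidence rate (0.0092), no prevalence gap between these countries is given, and B12 deficiency is described as above 40% across Latin America. Even those values are nearer to 1 than the detectable odds ratio of 1.6 at 40% prevalence.

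Finally, the intention to standardise procedures will reduce laboratory differences. It does nothing about true country differences in exposure.

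**Conclusion.** The point holds for the rule as stated. Sets matched only on age, gender and education, assayed in local laboratories and analysed with no stated centre term, would leave about 82–83% of pairs crossing countries and laboratories on Table 2 shares. Country and laboratory differences would then stay in the odds ratio.

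The size is conditional. With nearly uniform incidence, the null odds ratio lies roughly between 0.9 and 1.1. With a two-fold incidence difference and widely differing measured prevalence, it lies between about 0.8 and 1.3. A true odds ratio of 2.0 could appear as 1.77 to 1.94 if overall incidence is equal across countries while measured prevalence differs. These prevalences and the two-fold ratio are assumptions, and the illustrations in this range concern a common exposure such as B12 deficiency. The documents support neither a claim of large bias nor any fault in the 219, 657 and 876 counts or Table 4. The correction is nonetheless worth making before controls are drawn, because centre-specific incidence is one of the study's own questions and cannot be assumed uniform.

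**What to change.** In New biochemical assays, add centre (country) to age, gender and education as a matching factor, so that each set lies within one country and one laboratory. Preferably assay a case and its controls in the same batch. Matching also on urban or rural catchment area is optional where numbers allow.

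If sets are not formed within centre, say so, include centre in the conditional logistic model, and define deficiency with laboratory-specific calibration or cut-points.

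The cost is small but not nil. The sample stays at 219 + 657 = 876. The 36 to 46 available participants per case will thin once stored serum and the other matching factors are applied, so the age caliper may need widening for the oldest cases, which slightly loosens control of age. Centre main effects can no longer be estimated from the matched sets; incidence by centre still comes from the full cohort.
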